### **Ethics, data management and dissemination**

Patients will be screened for recruitment on the day prior to surgery, and the risks and benefits of the study will be explained. Written informed consent will be obtained from the patient. Patients may withdraw from the project at any time without prejudice. Study participants will be assigned a unique code as identifier throughout the study. All data will be entered into an electronic system by research team members who are trained in data entry. To ensure accurate data entry, a second member of the research team will check data entry. Data collection and study conduct will be monitored with the research team on weekly basis to ensure protocols are implemented consistently. All data will be kept confidential and maintained on a password-protected computer and in locked filing cabinets within the secure offices of the Department of Anesthesia and Intensive Care. Digital files will be securely deleted, and paper documents shredded, after 5 years. Only group data will be published. Access to data will be restricted to study investigators. Approval for the project has been obtained from The Joint Chinese University of Hong Kong-New Territories East Cluster Clinical Research Ethics Committee. The study will adhere to local laws, Declaration of Helsinki, International Council for Harmonization of Technical Requirements for Pharmaceuticals for Human Use Good Clinical Practice and Institutional Policies. All adverse events associated with the study drug will be recorded by the research team and reported to the trial management committee. The trial management committee, comprising external and independent clinicians, will review all events within 48 hours and discuss them at regular trial committee meetings. The results of this study will be disseminated at international conferences and in peer-reviewed journals.

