While regional anaesthesia is crucial for managing acute postoperative pain, its impact on CPSP remains largely unknown. The potential for regional anaesthesia to reduce CPSP has been identified as one of the top research priorities in anaesthesia and perioperative care. Intertransverse process block (ITPB) is a novel and promising alternative, targeting the paravertebral space through extra-paravertebral injection within the intertransverse tissue complex, posterior to the superior costotransverse ligament (SCTL). Recent MRI studies have demonstrated consistent spread of local anaesthetic to the ipsilateral intercostal, paravertebral spaces, neural foramina, and epidural space following ITPB, suggesting potential for both somatic and visceral analgesia. It demonstrated preferential spread of LA to the epidural space and neural foramina over the ESPB, and into the thoracic paravertebral space with effective analgesia after breast and video-assisted thoracoscopic surgeries. Compared to other regional techniques in cardiac surgery, ITPB may offer a simpler and safer approach with reduced risk of pleural puncture and bleeding. Therefore, this trial will assess the analgesic efficacy of ITPB aimed at mitigating both acute and chronic postsurgical pain in cardiac surgical patients. We hypothesis ITPB will reduce CPSP after cardiac surgery, improve pain control, improve quality of recovery and health-related quality of life. The primary aim is to investigate the efficacy of intertransverse process block (ITPB) on CPSP after cardiac surgery by determining the incidence of CPSP at 3-month, defined as persistent pain that was not present before surgery or that had different characteristics, and other possible causes of pain are excluded. The secondary aims are to investigate the quality of recovery after cardiac surgery, and its analgesic efficacy in the immediate postoperative period, and to investigate the efficacy of ITPB on the incidence of CPSP at 6-month and 12-month, and the pain interference (sensory and affective components, physical activities) at 3-month, 6-month and 12-month after surgery.

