### ***Ultrasound Block Placement***

The intervention group received bilateral ITPB after GA induction, whilst sham blocks are performed in the control group. All blocks are performed by an anaesthesiologist who had previously performed  $\geq 50$  successful ITPB blocks, using Philips EPIQ ultrasound system, with a curved array transducer (C5-1), and 80mm echogenic nerve block needle (SonoTAP; PAJUNK, Germany). ITPB is performed with the patients positioned in a lateral decubitus position. The target intervertebral level (T4-5) is identified and marked in the preview ultrasound scan. The transducer is placed 2-3 cm lateral to the spinous process. Under strict asepsis, a single-level (T4-5) ultrasound-guided ITPB is performed with the in-plane insertion of the block needle from lateral to medial direction until its tip is at the medial aspect of the retro-SCTL space. After confirming the needle position by distension of the retro-SCTL space after a test bolus injection of 1-2 ml 0.9% normal saline, 25 ml 0.25% levobupivacaine or placebo is injected via the nerve block needle in small aliquots. The same procedure is repeated on the other side with the same volume of study medication. The time required to perform the block will be recorded as the time from insertion of block needle to removal from the patient after injection.

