***Outcome measures***

Though acute pain is identified as an important predictor for the development of CPSP, advanced pain management strategies have failed to reduce the overall incidence of CPSP, suggesting a complex underlying mechanism. Evidence has demonstrated that pain-related functional interference and patient-reported outcomes, such as quality of recovery, might be associated with the development of CPSP. Thus, the primary outcome of this study is the Quality of Recovery (QoR-15) score at 24 hours after extubation. QoR is recommended for patient's comfort after surgery, and is highly valid and reliable patient-centred outcome measure.

Secondary outcomes include Numerical Rating Scale (NRS) pain scores at 2-hour, 4-hour, 8-hour, 12-hour, 24-hour, 48-hour and 72-hour after extubation, patient satisfaction with pain management and postoperative morphine consumption at the above time points, the time for first morphine rescue (in minutes), intraoperative opioids consumption (converted into morphine equivalence), duration of mechanical ventilation, length of stay in ICU and hospital, side effects associated with opioids such as postoperative nausea and vomiting (PONV), incidence of CPSP at 3-month, 6-month and 12-month, and pain interference measured with Short-Form McGill Pain Questionnaire-2 (SF-MPQ-2) and Brief Pain Inventory (BPI) Interference Scale at 3-month, 6-month and 12-month after surgery.

CPSP is defined as persistent pain after surgery that was not present before surgery or that had different characteristics, and other possible causes of pain are excluded. Participants reported CPSP will further be assessed on the severity and impact of chronic pain based on the recommendations by the Initiative on Methods, Measurement, and Pain Assessment in Clinical Trials (IMMPACT), including the SF-MPQ-2 to assess the sensory pain qualities and affective components, and the BPI to assess the interference of pain with physical functioning.

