### ***Data collection (Appendix A)***

After screening for eligibility, patients will be given information sheets regarding the main aspects of the trial and information will be discussed with the research nurse before informed consent is obtained. All data is collected by research team members blinded to group assignment. Patient demographics and body mass index are recorded. Cumulated opioid consumption data and time to first morphine rescue are extracted from PCA pump. At 2-hour, 4-hour, 8-hour, 12-hour, 24-hour, 48-hour and 72-hour post-extubation, pain scores at rest and on coughing are quantified using NRS from 0 to 10. Zero represents no pain at all while 10 points represents the worst pain ever. The patients are asked to rate the overall satisfaction to pain management on a verbal analogue scale (0=worst possible, 100=best possible) at the predefined points. Any nausea and vomiting, and use of rescue antiemetics are documented. The Chinese validated QoR-15 will be completed at baseline (preoperatively) and postoperatively at 24-hour and 72-hour after extubation. The SF-MPQ-2 and Brief Pain Inventory will be used to evaluate the CPSP at 3-month, 6-month and 12-month after surgery.

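### Adverse event recording is worded around the study drug, and no section collects complications of the block procedure that both arms undergo

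*Protocol*

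**What the plan says.** The rule on adverse events is in the Protocol, Ethics, data management and dissemination: "All adverse events associated with the study drug will be recorded by the research team and reported to the trial management committee". The next sentence has an independent committee review events within 48 hours. The same section commits the trial to Good Clinical Practice in general terms.

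Under Ultrasound Block Placement, the intervention group has a bilateral block, "whilst sham blocks are performed in the control group". The injection is described for both arms together: "25 ml 0.25% levobupivacaine or placebo is injected via the nerve block needle in small aliquots". Then: "The same procedure is repeated on the other side with the same volume of study medication". The only item about the block that this section says will be recorded is how long it took.

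On hazards, the Introduction links epidural anaesthesia to neuraxial haematoma under anticoagulation, and paravertebral blocks to pneumothorax and pleural puncture. It then says of the study block: "Compared to other regional techniques in cardiac surgery, ITPB may offer a simpler and safer approach with reduced risk of pleural puncture and bleeding".

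The harms collected by name are opioid side effects. Data collection (Appendix A) adds: "Any nausea and vomiting, and use of rescue antiemetics are documented".

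**The concern.** The recording rule is tied to the drug, whereas part of the hazard comes from the needle. A pleural puncture, a pneumothorax or a block-site haematoma is caused by needle placement and would happen with saline as easily as with levobupivacaine. Someone applying the sentence literally has to judge cause before recording. After a sternotomy, a pneumothorax or a bleed is readily put down to the operation.

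What is at stake is the trial's description of the harms of the technique it studies. This cannot be left to an analysis plan, because an analysis cannot recover events that were never collected. A report of no complications would then be hard to interpret: it could mean that none occurred or that none was looked for.

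**Working it through.** **Step 1. Set the rule against the procedure and the data lists.**

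| Place in the Protocol | What it covers | Block complications named? |
|---|---|---|
| Ethics, data management and dissemination | Events associated with the study drug; committee review | No |
| Ultrasound Block Placement | Technique; block time | No |
| Outcome measures | Opioid side effects such as nausea and vomiting | No |
| Data collection (Appendix A) | Nausea, vomiting, rescue antiemetics | No |
| Appendix A, list and schedule | Nausea, vomiting, antiemetics; length of stay | No |

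No section fills the gap left by the drug-related wording.

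**Step 2. Ask whether randomisation would expose the harm.** As described, controls have the needle placed and placebo injected on both sides. If the complication rate due to the needle is p in each arm, the expected difference is p − p = 0, whatever p is. Needle harm therefore has to be read from counts, not from a contrast between arms.

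**Step 3. What complete recording could show.** The plan states no figure for harms, so there is none to reproduce. The inputs are the planned 96 patients, 48 per group (Statistics and sample size calculation). With no event among n patients, the exact one-sided 95% upper limit is 1 − 0.05^(1/n):

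- n = 96: 1 − 0.05^(1/96) = 0.0307, about 3.1%
- n = 48: 1 − 0.05^(1/48) = 0.0605, about 6.1%

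**Step 4. Chance of seeing any event.** The documents give no complication rate, so a range is assumed. The chance of at least one event in 96 patients is 1 − (1 − p)^96:

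| Assumed rate p | Chance of at least one event |
|---|---|
| 0.5% | 38% |
| 1% | 62% |
| 2% | 86% |
| 5% | 99% |

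**Step 5. Limits of a comparison.** Even for a harm that could differ between arms, such as a reaction to the local anaesthetic, 48 per arm gives 21% power for 1% against 5% and 49% for 1% against 10% (assumed rates). The output is descriptive.

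**The case against.** The strongest reply is that the sentence says what will be recorded and does not forbid recording anything else. Nausea and vomiting are documented whatever their cause, the trial is committed to Good Clinical Practice, and the committee is said to review all events. The case report form is not shown and might already carry such items. This stands as far as it goes: it cannot be said that needle harms *will* be missed. But a general commitment does not replace the specific operating sentence, and the reference to all events follows on from it.

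Four stronger readings are tempting, and the documents do not support them.

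- *The recording rule is why the trial cannot test its safety rationale.* That rationale ("ITPB may offer a simpler and safer approach with reduced risk of pleural puncture and bleeding") is a hedged background remark comparing the block with other regional techniques. None of those is an arm, and safety is not a stated aim. Perfect recording would leave that comparison untested.
- *Control-arm harms are less likely to be attributed to the drug.* The block operator, the care team and the data collectors are all blinded, so they have no basis for attributing events differently by arm.
- *There is no usable harm comparison.* Harms of levobupivacaine against placebo are what the present sentence covers. Needle harms would not appear in a comparison under any recording rule.
- *All 96 × 2 = 192 placements fall outside the rule.* This takes the sentence as excluding everything else, which it does not say.

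It is also fair to object that sending every event after cardiac surgery to a committee with a 48-hour review duty would be a real burden. That stands, and it argues for a narrow remedy.

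**Conclusion.** The point holds as a gap in the stated rule. Recording and committee reporting are worded around the drug, nothing else in the protocol collects block complications, and so needle-related harms can go unrecorded in both arms.

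The size is modest. What may be lost is a descriptive complication count. If that count were zero, it would carry an upper limit of about 3.1% (96 patients pooled) or 6.1% (one arm of 48). The primary comparison of QoR-15 at 24 hours is not threatened. This is a cheap improvement to the safety data, not a flaw in the main result.

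The limits assume that all planned patients have the block and a completed checklist. Pooling assumes that the sham involves the same needle placement, as Ultrasound Block Placement describes. It does not suit local anaesthetic reactions, where only the 48 patients given levobupivacaine are exposed to the study injection of the drug.

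**What to change.** 1. Reword the sentence in Ethics, data management and dissemination so that recording and reporting cover adverse events associated with the study drug *or the block procedure*, in both arms.
2. Add a short fixed checklist, completed for every patient regardless of judged cause: pleural puncture, pneumothorax, block-site bleeding or haematoma, and suspected local anaesthetic reaction. Assess relation to drug, procedure or surgery afterwards, blind to allocation.
3. List these complications under Outcome measures as a descriptive safety outcome, with counts by arm and pooled over both arms and exact confidence limits.

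The cost is one sentence and one form page. Some events due to the operation will be recorded, and the blinded assessment afterwards deals with those. Routine events after cardiac surgery that are not on the checklist need not go to the 48-hour committee review. The change has to be in place before the data are collected.

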## Appendix A

The following medical and surgical data during the hospital stays will be extracted from electronic record:

1. Patient demographics (age, gender, EuroScore)
2. Type of surgery
3. Duration of surgery and duration of cardiopulmonary bypass
4. ASV time to spontaneous breathing
5. Episodes of nausea and vomiting, and use of rescue antiemetics
6. Length of ICU and hospital stay

|                     |           | STUDY PERIOD    |             |             |             |              |              |              |              |         |         |
|---------------------|-----------|-----------------|-------------|-------------|-------------|--------------|--------------|--------------|--------------|---------|---------|
|                     | Enrolment | Post-allocation |             |             |             |              |              |              |              |         |         |
| TIMEPOINTS          | Baseline  | 2h extubate     | 4h extubate | 6h extubate | 8h extubate | 12h extubate | 24h extubate | 48h extubate | 72h extubate | 3-month | 6-month |
| ENROLMENT:   |           |                 |             |             |             |              |              |              |              |         |         |
| Eligibility screen  | X         |                 |             |             |             |              |              |              |              |         |         |
| Informed consent    | X         |                 |             |             |             |              |              |              |              |         |         |
| Demographic data    | X         |                 |             |             |             |              |              |              |              |         |         |
| Comorbidity data    | X         |                 |             |             |             |              |              |              |              |         |         |
| EuroScore           | X         |                 |             |             |             |              |              |              |              |         |         |
| Allocation          | X         |                 |             |             |             |              |              |              |              |         |         |
| INTERVENTION |           |                 |             |             |             |              |              |              |              |         |         |
| ITPB                | X         |                 |             |             |             |              |              |              |              |         |         |
| OUTCOMES:    |           |                 |             |             |             |              |              |              |              |         |         |
| Presence of CPSP    |           |                 |             |             |             |              |              |              |              | X       | X       |
| SF-MPQ-2            |           |                 |             |             |             |              |              |              |              | X       | X       |

|                                           |   |   |   |   |   |   |   |   |   |   |
|-------------------------------------------|---|---|---|---|---|---|---|---|---|---|
| BPI                                |   |   |   |   |   |   |   |   | X | X |
| QoR-15                             | X |   |   |   |   | X |   | X |   |   |
| Intraoperative morphine equivalent |   | X |   |   |   |   |   |   |   |   |
| NRS score                          |   | X | X | X | X | X | X | X |   |   |
| ASV time to spontaneous breathing  |   | X |   |   |   |   |   |   |   |   |
| Time to first morphine rescue      |   | X | X | X | X | X | X | X |   |   |
| Postoperative morphine consumption |   | X | X | X | X | X | X | X |   |   |
| Patient satisfaction               |   | X | X | X | X | X | X | X |   |   |
| Use of rescue antiemetics          |   | X | X | X | X | X | X | X |   |   |
| Nausea/vomiting                    |   | X | X | X | X | X | X | X |   |   |
| ICU and hospital stay              |   |   |   |   |   |   |   |   | X |   |

**Appendix A** Assessments overview. NRS, numerical rating scale; ASV, adaptive support ventilation; QoR-15, Quality of Recovery questionnaire; BPI, Brief Pain Inventory; SF-MPQ-2, Short-Form McGill Pain Questionnaire
